### Participant recruitment

Twenty-five patients with depression (either unipolar or bipolar depressive episode) will be recruited from the Barnes-Jewish Hospital inpatient floors or the ECT-outpatient referral service. Consulting ECT psychiatrists will interview potential participants to determine diagnosis, eligibility, and interest in the study. As per routine practice, Diagnostic and Statistical Manual of Mental Disorders (DSM-5) criteria will be utilized by the ECT clinician in determining the diagnosis. Suitable study candidates will be referred by ECT psychiatrists to study coordinators. Informed consent will be obtained. Once enrolled, study participants will receive a paper consent form and study material directing participants to the ClinicalTrials.gov record.^1^

### Clinical assessments

Two clinical assessments will be done throughout this study, the QIDS-SR16 (Quick Inventory of Depressive Symptomatology-16 Self Report), and the PSQI (Pittsburgh Sleep Quality Index). The QIDS-SR16 measures the participant’s depressive symptoms over the past seven days (86). At our institution, patients receiving ECT typically complete QIDS-SR16 throughout their ECT course. While other scales for measuring depression severity exist, such as Hamilton Depression Rating Scale (HAMD) and Montgomery–Asberg Depression Rating Scale (MADRS), the usage of QIDS-SR16 in the ECT suite has been historically chosen because it is a patient-reported assessment that accommodates for the high volume of participants in the suite limited clinician resources. The questionnaire includes 16 questions that survey nine symptom domains: sad mood, self-criticism, poor concentration, suicidal ideation, anhedonia, energy, sleep disturbance, appetite, and psychomotor agitation. Paper versions of the QIDS-SR16 will be completed by participants prior to each ECT session. The PSQI is a scoring system to assess sleep quality and habits during the past month (87). The assessment measures seven components of sleep: subjective sleep quality, sleep latency, sleep duration, sleep efficiency, sleep disturbances, sleeping medications, and daytime dysfunction. PSQI will be obtained *via* an electronic form administered prior to the first ECT session. Suicidality will be assessed by psychiatry physicians in the ECT suite, as per standard of care.

### Electroconvulsive therapy

Electroconvulsive therapy will be delivered using standard-of-care clinical protocols. Three stimulation electrode placements will be utilized: right unilateral (electrodes placed on the right temple and vertex of the head), bilateral (electrodes placed on the right and left temple), and bifrontal (both electrodes placed on the forehead, above the outer canthus of the eye).

Prior to ECT stimulation, general anesthesia will be induced. Commonly used regimens include etomidate 0.2 mg/kg, methohexital 1 mg/kg, or ketamine 1.5 mg/kg. The anesthetic regimen will be determined at the anesthesiologist’s discretion. Standard American Society of Anesthesiologists safety monitoring will occur throughout treatment.

The ECT stimulation will be delivered *via* routine clinical practice, using the Thymatron System IV. On the initial treatment (dose titration) session, ECT-naïve individuals typically receive right unilateral ECT titration at 5% charge, 0.3 ms pulse-width, 40 Hz frequency. While a seizure duration of 20–25 s has been accepted to be adequate by some, there are no firm data that support this position. Instead, seizure duration appears to not determine adequacy of response (88–93). Therefore, at our institution seizure duration is not used to determine adequacy of the treatment. Instead, a seizure duration of 10 s is defined as a reasonable minimal limit for determining the presence of an induced seizure. If an appropriate seizure is not obtained after this initial stimulation, then ECT charge will be increased in a protocolized fashion until a seizure of at least 10 s is obtained. Subsequent right unilateral treatments are then administered at a charge sixfold above seizure threshold.

If, based upon the clinical judgment of the ECT clinician, right unilateral ECT at sixfold seizure threshold does not improve depressive symptoms, participants may then transition to 100% right unilateral charge and if need be bilateral ECT at two-times seizure threshold. If during the course of ECT seizure duration becomes less than 10 s, then modifications, based on the exact clinical situation will be made by the ECT psychiatrist in how ECT is provided in order to increase duration to above 10 s.

Per hospital protocol, if individuals experience cognitive impairment based on routine clinical evaluation with right unilateral or bilateral ECT during thrice a week sessions, ECT treatments may be performed twice a week (94). Cognitive impairment determined during routine clinical practice will be based on history and bedside clinical examination. If cognitive complications do not resolve at a twice a week frequency, right unilateral or bilateral ECT is transitioned to bifrontal ECT at the discretion of the clinical care team.

### High-density electroencephalography recordings during electroconvulsive therapy sessions

A high-density EEG recording system will be used to record signals before and after ECT charge delivery. A Net Amps 400 amplifier and Net Station software version 5.0 (Magstim, Eden Prairie, MN, USA) will be used to acquire EEG data sampled at 500 Hz. A network camera (Axis P3364LV, Axis Communications, Lund, Sweden) will be used to video record seizures during EEG recordings. Modified 64-channel GSN electrode caps (Magstim, Eden Prairie, MN, USA) will be used to ensure that ECT stimulation electrodes are appropriately placed for the procedure. Electrode sensors will be filled using electrode Elefix Ag/AgCl paste (Elefix, Nihon Kohden America, Inc., Irvine, CA, USA), to keep electrode impedances less than 100 kΩ per channel. Electrode sensors may be omitted if location will impact stimulation electrode placement (GSN E1, E4, and E54 during right unilateral ECT, E1, and E17 during bilateral ECT, E5, and E10 during bifrontal ECT).

Prior to induction of general anesthesia, separate 5-min recordings will be obtained for eyes-closed and eyes-open conditions. The EEG cap will be disconnected from the acquisition computer during electrical stimulation to protect the electrical equipment. After the ECT stimulus is delivered, the EEG cap will be reconnected. Our group has found that this method of disconnecting the cap generally leads to 1–2 s of lost data; this is comparable to the time of data lost using the standard 2-lead Thymatron IV System.

### Longitudinal recording of sleep electroencephalography using wireless wearable devices

Second-generation Dreem headbands will be used to acquire at-home unattended overnight sleep EEG recordings. The device has four frontal EEG electrodes [Fp1, Fp2 (ground), F7, and F8] and two occipital sensors (O1 and O2). The device has an infrared light source and sensor to measure heart rate. A three-axis set of accelerometers in the device allows monitoring of movement patterns that aid in sleep staging, arousal detection, and determination of respiratory effort. In the perioperative setting, this device provides adequate signals for detecting sleep spindles and sleep slow waves, with a single night sufficient for establishing baseline sleep macrostructure (27).

In addition to the Dreem headband, the option of wearing a wrist actigraphy device will be offered to allow evaluation of changes in circadian rhythms in a prespecified sub-study. ActTrust 2 wrist actigraphs (Condor Instruments, São Paulo, Brazil) will be utilized to collect longitudinal measures of rest and activity. These data will complement the longitudinal Dreem data and provide additional insight into sleep and circadian rhythm changes throughout ECT.

### Manual sleep scoring

Sleep EEG recordings will be imported and preprocessed using custom MATLAB (MathWorks, Natick, MA, USA) scripts and EEGLAB (95). Signals will be 0.5–50 Hz bandpass filtered and downsampled to 250 Hz. EEG signals and Dreem accelerometry respiratory effort waveforms will be exported in European Data Format (EDF). American Academy of Sleep Medicine (AASM) certified sleep technologists will then stage recordings using Philips Respironics Sleepware G3 Software and modified AASM scoring rules developed for use on single frontal EEG channel recordings (96, 97).

### Characterization of electroencephalography sleep microstructure

Custom-written MATLAB scripts will be utilized to compute sleep SWA and spindle density during 30-s epochs of N2 and N3. Sleep SWA will be calculated as an average of 0.5–4 Hz EEG power per minute during N3 sleep. As a secondary analysis, SWA during both N2 and N3 will be calculated. Dissipation of SWA over the overnight sleep will be evaluated through combining all NREM epochs, normalization of total sleep time by dividing total NREM length in quintiles, and comparison of SWA during the first and last quintiles (98). Spindle density will be quantified as the number of spindles per minute of N2 sleep. As a secondary analysis, spindle density for both N2 and N3 will be calculated. A semi-automated algorithm will be used to detect sleep spindles. This algorithm will be optimized based on partial manual scored spindles by registered polysomnographic technologists using AASM guidelines.

### Quantitative measures of electroconvulsive therapy-induced seizure markers

Recordings of ECT-induced seizures will be visually inspected and processed in Net Station Waveform Tools (Magstim, Eden Prairie, MN, USA). Data will be bandpass filtered at 1–100 Hz. Channels with excessive noise will be interpolated. Following previously established criteria (99), seizures will be staged across three phases by experienced epileptologists using Persyst software (Persyst, Solana Beach, CA, USA). Data from Phase 3, with rhythmic 2.5–3.5 Hz spike/polyspike-wave activity, will be utilized for CPC analysis using EEGLAB (95) in MATLAB. Custom MATLAB scripts will employ an automatic algorithm which will be utilized to detect large amplitude CPCs based on the difference between average suborbital facial electrode signals and Cz electrode (82). Cumulative duration of CPCs will be computed for each ECT session.

### Statistical analysis

Linear mixed-effects models will be constructed to account for missing data without the need for data imputation or deletion. Models will be generated in MATLAB. To characterize SWA over the course of ECT, linear mixed-effect models will be constructed using SWA as a dependent variable and treatment number as an independent variable. Similarly, to examine sleep spindle density changes, linear mixed-effects models will be generated that have sleep spindle density as a dependent variable and treatment number as an independent variable. Associations between CPC and sleep SWA or sleep spindles will be evaluated *via* respective linear mixed-effect models. For all aims, separate models will be constructed for responder and non-responder groups. QIDS-SR16 scores and ECT stimulation *parameters* will be entered as covariates for all analyses, as appropriate.

A total number of 25 participants will be targeted for recruitment in this study. Sample size calculations are based on the published data following conventions for statistical power analysis in the behavioral sciences (100) and our best guesses regarding effect size and SD. The main factor that we considered in estimating our required sample size was based on reported changes in SWA measure in major depression (98, 101, 102). We estimate a medium effect size and a partial η^2^ value of 0.1. Thus, we estimate sample sizes of 17 (power of 0.8, alpha of 0.05) based on a conservative assumption on the number of treatments (10 treatments) to account for missing a session or poor quality of EEG data. Participants may withdraw from the study at any time, and we will track reasons for patient attrition. Given that a previous study on a similar patient population cohort conducted at Barnes-Jewish Hospital and Washington University showed a 30% attrition rate (80), we expect to have at least 17 participants with interpretable data in the current study.

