## Introduction

### Electroconvulsive therapy: An effective treatment for depression but with unclear underlying mechanisms

Electroconvulsive therapy (ECT) is an effective treatment for major depressive disorder (MDD), a common illness ranking as the second leading cause of disability worldwide (1). During ECT, a brief electrical stimulus is delivered through the scalp to elicit a generalized seizure under general anesthesia. Two to three ECT sessions are administered per week during the index treatment course. Compared to oral antidepressants, ECT ameliorates depressive symptoms rapidly; some individuals experience improvement shortly after the third treatment (2). The response rate to ECT for a depressive episode is up to 80% (2–4), with remission rates ranging from 50 to 63% (5, 6).

Electroconvulsive therapy was used for the first time on a human patient in 1938 by Cerletti and Bini (7). Although ECT has been used for over 80 years, many unknowns remain. It is thought that ECT induces neuroplasticity and alters neural connectivity within functional networks; however, these networks have yet to be elucidated (8, 9). Moreover, it remains unclear why certain patients do not respond to therapy. Prognostic physiologic biomarkers are not routinely used to predict and monitor ECT response. Identifying such biomarkers may aid clinicians in referring the right candidates for ECT or adapting ECT parameters (i.e., charge and electrode placement) to improve treatment response.

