**FIGURE 3 F3:**
[figure not shown]
PICOT (participants, intervention, control, outcomes, timing) summary of study design. This study will recruit adults requiring ECT treatment for a depressive episode. Participants will wear a Dreem headband at night to obtain sleep EEG recordings throughout the course of ECT. High-density EEG recordings will also be obtained during ECT sessions to assess central positive complexes (CPCs). The primary outcomes of CET-REM include characterization of slow wave activity and sleep spindle density throughout ECT course.

Each enrolled participant will undergo an index course of ECT, following standard clinical care. Self-reported depressive scores will be assessed prior to each ECT session to determine response, and the total number of treatments will be determined by the psychiatrist performing ECT, as part of routine clinical practice. Response to the ECT will be defined as a 50% reduction of baseline QIDS score. Sleep structure on the nights of ECT sessions would be confounded by the effects of the anesthetic used in the procedure. Thus, ambulatory overnight sleep EEG data will be acquired *via* a Dreem device on post-ECT days. For exploratory analyses, optional high-density EEG data will be recorded during ECT-induced seizures. Our study design will allow us to longitudinally collect a large data set of EEG markers, including sleep slow waves, sleep spindles, and CPCs.

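### Every planned model is split by responder status, but response has no fixed time point and about 30% attrition is expected, so the no-imputation, no-deletion claim does not extend to the grouping variable

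*Protocol article*

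**What the plan says.** All references are to the protocol article.

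- **Missing data (Statistical analysis).** "Linear mixed-effects models will be constructed to account for missing data without the need for data imputation or deletion".
- **Grouping (Statistical analysis).** "For all aims, separate models will be constructed for responder and non-responder groups". Both specific aims and the exploratory aim, under Objectives and specific aims, repeat this split. No model for the whole cohort is described.
- **Definition of response (Study design, text after Figure 3).** "Response to the ECT will be defined as a 50% reduction of baseline QIDS score". No session or date is attached to it.
- **When depression is scored (same place).** "Self-reported depressive scores will be assessed prior to each ECT session to determine response".
- **Length of the course (same place).** "the total number of treatments will be determined by the psychiatrist performing ECT, as part of routine clinical practice".
- **Expected loss (Statistical analysis).** A previous study in a similar population "showed a 30% attrition rate". From 25 recruits the plan therefore expects no fewer than 17 with usable data.
- **Routine scoring (Clinical assessments).** At this site, "patients receiving ECT typically complete QIDS-SR16 throughout their ECT course".

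**The concern.** A linear mixed model uses whatever outcome values a participant has, so a missed night of SWA or spindle data does not remove that participant. The responder label is different. It is not an outcome in the model; it decides which model the participant enters. The mixed model can neither supply a missing label nor correct one that reflects a shortened observation period.

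Two consequences follow. A participant who stops being observed before reaching a 50% reduction may be placed with the non-responders only because observation ended. A participant who cannot be placed at all contributes to no planned analysis, however many good nights were recorded.

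The article's Conclusion says the study will shed light on markers of responsiveness to ECT, so readers will compare the two sets of slopes. If group membership partly reflects retention, so does that comparison.

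**Working it through.** **1. The plan's own figures.** Recruits 25, attrition 30%: 25 × 0.70 = 17.5, which agrees with the stated minimum of 17. The required 17 also reproduces approximately. With partial η² = 0.1, f² = 0.1/0.9 = 0.111; a one-group repeated-measures F test with 10 measurements, alpha 0.05 and power 0.8 needs 16 to 18 participants, depending on the noncentrality convention (taking zero correlation where the convention needs one). These figures are not in dispute. Expected loss is 25 × 0.30 = 7.5, that is 7 to 8 people.

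**2. What the label depends on.** Take a hypothetical participant who leaves after four sessions with a 25% reduction.

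- *Last available score:* non-responder. An early score stands in for the course outcome, which is imputation in effect.
- *50% reached at any session:* non-responder, with fewer chances to qualify than someone followed for ten sessions.
- *Score at the end of the course:* unknown unless later scores are obtained. If unknown, the participant enters neither model, which is deletion.

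The article's definition is compatible with all three rules. A participant who had already reached 50% before leaving could be a responder under the first two.

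**3. Upper bound on the headcount.** Let D = 7.5 lost, C = 17.5 remaining and r = response rate among those remaining. If all D contributed nights and were classed as non-responders, their share of that group is D / [D + C(1 − r)]. The article's Introduction gives a response rate of up to 80%; the lower values are assumptions.

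| r | Non-responders among those remaining | Share made up of those lost |
|---|---|---|
| 80% | 17.5 × 0.20 = 3.5 | 7.5/11.0 = 68% |
| 60% | 17.5 × 0.40 = 7.0 | 7.5/14.5 = 52% |
| 50% | 17.5 × 0.50 = 8.75 | 7.5/16.25 = 46% |

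With 7 or 8 lost instead of 7.5, the range is 44% (7/16.0) to 70% (8/11.4). Those lost are the majority only when C(1 − r) < D, so r > 1 − 7.5/17.5 = 57%.

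**4. If half of those lost had already responded.** D falls to 3.75. The share is 3.75/(3.75 + 3.5) = 52% at r = 80% and 3.75/(3.75 + 8.75) = 30% at r = 50%.

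**5. If those lost are left out.** About 14 responders and 3.5 non-responders remain at r = 80%, or 8.75 of each at r = 50%.

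**6. Headcount is not weight.** In a random-intercept model with equally spaced sessions, a participant's within-person information on the slope is proportional to the sum of squared deviations of session number. Sessions 1 to 4 give 2.25 + 0.25 + 0.25 + 2.25 = 5; sessions 1 to 10 give 10 × 99/12 = 82.5. At r = 80%, if everyone lost left after four sessions, they supply 7.5 × 5 = 37.5 against 3.5 × 82.5 = 288.75 from the others: 37.5/326.25, or about 12%, compared with 68% by headcount. Random slopes would raise this share. The article does not state the random-effects structure.

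**The case against.** The strongest reply is that QIDS is scored before every session expressly to judge response, and that nothing requires a completed course. An early leaver has scores and can be classified; the Introduction notes that some patients improve shortly after the third treatment. This stands. A reader might infer that responder status needs a full course, so that everyone who leaves must be either deleted or counted as a non-responder. The article does not say so, and a third outcome, responder, is open. What the reply does not remove is the dependence on length of observation for those who leave before reaching 50%.

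Second, the missing-data sentence can be read as the usual remark about incomplete repeated outcomes, and a rule for withdrawals may sit in a full protocol or analysis plan that is not shown. The absence of such a rule is not the point here. The sentence is stated without that limit, alongside models that all need the label.

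Third, the 30% comes from another study and is not defined as stopping ECT early. Some of those lost may continue ECT and routine QIDS scoring, so their label is recoverable; others may have no usable EEG and enter no model anyway. This stands, and it is why the headcount above is only an upper bound. The plan also budgets for the loss and will track reasons for attrition.

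Fourth, a reader might infer that early leavers flatten the non-responder slope and so create a difference between the groups. That does not follow. Under a linear trend, seeing only early sessions makes a slope less precise, not flatter; flattening would need delayed change, which the article does not assert. If would-be responders change more and are mislabelled as non-responders, the groups become more alike. The article also specifies no formal contrast between them.

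**Conclusion.** The point holds in a limited form and should be corrected. All planned models depend on a label with no fixed time point, in a study that expects to lose about 7 to 8 of 25 participants. The claim of needing neither imputation nor deletion is sound for missing SWA and spindle values and unsupported for the grouping variable.

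The possible size is 46% to 68% of the non-responder group by headcount. This assumes 7.5 lost, all with usable nights, all classed as non-responders, and a response rate of 50% to 80% among the rest. It should not be read as a finding that the group will consist mostly of people who left: that fails below a response rate of about 57%, and the share in slope information may be nearer 12% under the assumptions shown. The direction of bias is not established.

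**What to change.** 1. Define response at the end of the clinical ECT course from the routine QIDS-SR16. On the article's schedule, the last such score is the one taken before the final treatment.
2. Retrieve those scores even when headband wear or high-density EEG has stopped, with consent if existing consent does not already cover it.
3. Label participants without an end-of-course score undetermined; do not make them non-responders by default.
4. Fit a whole-cohort slope model for SWA and for spindle density that keeps every usable night, alongside the two group models.
5. Limit the missing-data sentence to missing outcome values, and say how undetermined participants enter the analysis.

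The cost is a few sentences of text, possibly one sentence in the consent form, and chart retrieval of a score that the site typically collects. No new visits or measurements are needed. The downside is a smaller labelled non-responder group, perhaps 3 to 4 people at an 80% response rate if no further scores can be retrieved for those lost.

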### Objectives and specific aims

The primary objective of our study is to longitudinally track changes in sleep microstructure throughout the ECT course of a convenience sample of patients, who are clinically ascertained and treated for depressive episodes on a busy hospital-based service. Wearable dry-electrode EEG devices will be utilized to monitor overnight sleep at home. High-density EEG during the ECT procedure will allow characterization of seizure markers. Specific aims, hypotheses, and analytical approaches are listed below.

#### Specific aim 1

Assess changes in N2 and N3 sleep SWA over the course of serial ECT sessions. We hypothesize SWA will increase over the course of ECT. Separate linear mixed effects models will be constructed to assess SWA changes in responder and non-responder groups.

#### Specific aim 2

Evaluate changes in sleep spindle density during N2 and N3 sleep over the course of ECT. We predict that there will be an increase in sleep spindle density throughout ECT. Separate linear mixed effects models will be constructed to assess changes in sleep spindle density in responder and non-responder groups.

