## Conclusion

The CET-REM study will probe longitudinal changes in sleep microstructure and seizure markers over the index course of ECT. Wireless wearable devices will be utilized for at-home unattended collection of sleep EEG to provide measures of sleep slow waves and sleep spindles. ECT-induced seizure markers will be assessed using high-density EEG recordings. Overall, the results from this study will elucidate underlying mechanisms and markers for responsiveness to ECT.

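### Every aim is analysed in separate responder and non-responder models with no stated contrast between them, so the analysis as written does not support a claim about markers of ECT response

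*Protocol article*

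**What the plan says.** Under Specific aim 1 the article says "Separate linear mixed effects models will be constructed to assess SWA changes in responder and non-responder groups". Specific aim 2 and the Exploratory aim are worded in the same way. The Statistical analysis section first describes the model without any split: "linear mixed-effect models will be constructed using SWA as a dependent variable and treatment number as an independent variable", with a parallel model for spindle density. It then adds "For all aims, separate models will be constructed for responder and non-responder groups". QIDS-SR16 scores and stimulation parameters "will be entered as covariates for all analyses, as appropriate".

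The Study design section defines the groups: "Response to the ECT will be defined as a 50% reduction of baseline QIDS score". No section gives a response-by-treatment-number term, a contrast of the two slopes, or a model with response group as predictor or outcome.

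On purpose, the Objectives section says "The primary objective of our study is to longitudinally track changes in sleep microstructure throughout the ECT course", and the stated hypotheses are increases over the course (Aims 1 and 2) and a correlation with CPC duration (Exploratory aim). The study's name links ECT response to EEG markers, and the Conclusion says "the results from this study will elucidate underlying mechanisms and markers for responsiveness to ECT". The sample size is justified by a medium effect, partial eta-squared 0.1, 10 treatments and "we estimate sample sizes of 17 (power of 0.8, alpha of 0.05"), with 25 recruited to cover 30% attrition.

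**The concern.** To call an EEG change a marker of response, one needs evidence that the change differs by response. Two slope tests in two separate sets of patients do not provide it. They leave the reader to note that one p-value is below 0.05 and the other is not, and that is not a test of a difference. When the groups differ in size, the smaller one will often miss significance for want of patients alone. The Introduction gives a response rate of up to 80%, so a small non-responder group is plausible. A response marker could then be reported where none exists.

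There is a second consequence. Aims 1 and 2 predict a rise over the course without restriction to either group, but the models named for them are split, which costs power for the main hypotheses.

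**Working it through.** **1. The plan's own figure.** Inputs from Statistical analysis: partial eta-squared 0.1, so f² = 0.1/0.9 = 0.111; m = 10 treatments; alpha 0.05; power 0.80. For a one-group repeated-measures F test, df1 = 9 and df2 = 9(N − 1).
- Noncentrality f²·N·9: N = 17 gives 0.111 × 17 × 9 = 17.0 and power 0.812; N = 16 gives 0.781. The required N is 17.
- Noncentrality f²·(N − 1)·9: power is 0.782 at 17, and the required N is 18.
- Attrition: 17/0.70 = 24.3, rounded up to 25.

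The planned 17 and 25 therefore reproduce, for one undivided group.

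**2. Slope model.** Treat each patient's slope as one observation with SD 1. The mean slope d giving 80% power in a two-sided one-sample t-test at n = 17 is d = 0.724. This ties the check to the plan's own power.

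**3. Splits (assumed).** A response rate of 80% gives 0.8 × 17 = 13.6, so 13/4 or 14/3. The 11/6 and 9/8 splits represent lower response rates.

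**4. Same true slope in both groups.** The groups contain different patients, so P(significant in responders only) = power(R) × [1 − power(NR)].

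| Split R/NR | Power R | Power NR | Responders only |
|---|---|---|---|
| 14/3 | 0.707 | 0.118 | 0.707 × 0.882 = 0.62 |
| 13/4 | 0.669 | 0.177 | 0.669 × 0.823 = 0.55 |
| 11/6 | 0.582 | 0.302 | 0.582 × 0.698 = 0.41 |
| 9/8 | 0.480 | 0.424 | 0.480 × 0.576 = 0.28 |

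Simulation (200,000 runs) gave 0.62, 0.41 and 0.28 for 14/3, 11/6 and 9/8. A direct two-sample comparison of slopes rejected in 0.05 at each of these splits.

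**5. Same check with the F test of step 1** (noncentrality f²·(n − 1)·9). Power is 0.67 and 0.10 at 14/3, 0.52 and 0.24 at 11/6, and 0.41 and 0.35 at 9/8. Significance in responders only then occurs in 60%, 40% and 26%. No group keeps the planned 0.80.

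**6. What a direct contrast could detect.** Suppose responders have slope 0.724 and non-responders 0. A two-sample t-test has noncentrality 0.724/√(1/a + 1/b) on 15 df. Power is 0.19 at 14/3, 0.22 at 13/4, 0.27 at 11/6 and 0.29 at 9/8. For 80% power, about 63 evaluable patients are needed at a near-even split and about 106 at 14:3. At 30% attrition that is 63/0.70 = 90 and 106/0.70 = 151.4, so 152 recruited.

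**7. Sensitivity to equal variances.** If the slope SD in non-responders is twice that in responders and the means are equal, the pooled two-sample test rejects in about 0.20 at 14/3 and 0.17 at 13/4 (100,000 runs).

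**The case against.** **The study is mainly descriptive.** The primary objective is to track change, and no stated hypothesis compares responders with non-responders. This stands: the descriptive objective is unaffected. The study's name and the Conclusion still go further than description.

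**A reader might infer that the study cannot show any relation to response.** The documents do not support that. Two separate models yield two slopes with standard errors from different patients, which could be contrasted, and the same data would fit a pooled model. What is absent is a stated contrast.

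**QIDS-SR16 is already in the models.** It is, as a covariate where appropriate. Within a group it can show an association between symptom level and the EEG measure. It does not compare change between groups, and it adjusts for the scale that defines them.

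**A reader might infer that the rise is never tested in the whole sample.** The Specific aims make this the likelier reading, but not the only one. The Statistical analysis section describes unsplit models before adding the separate ones, and the sample size fits a single group. The fair criticism is that the text is unclear.

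**The false inference is assumed.** No section says that the two p-values will be compared. The percentages also need a real common slope: with none, the figure is 0.05 × 0.95 = 4.75% at any split. This stands as a condition on the figures. No other comparison is offered, however, and a common rise is what Aims 1 and 2 predict.

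**A reader might add a multiplicity charge** for two outcomes in two groups: 1 − 0.95⁴ = 18.5%. That assumes four independent tests, whereas both outcomes come from the same patients. Such control is commonly left to the analysis plan, so it is not part of this point.

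**Conclusion.** The concern holds for the analysis as written. The split into separate models is stated for every aim, so it is a fixed choice and not a detail left to another document. It does not support the statement about responsiveness in the Conclusion.

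Read through separate p-values, identical slopes would look like a responder-only effect in 28% to 62% of studies across the splits examined. That range rests on 17 evaluable patients, assumed splits from 9/8 to 14/3, equal slope variance, and a standardised slope of 0.724. A direct contrast would err in 5% under the same assumptions. The split models are also not the analysis for which 17 was calculated.

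A direct contrast corrects the logic but not the precision. At 17 evaluable its power is about 0.19 to 0.29, so any statement about response must remain exploratory.

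**What to change.** 1. Fit one mixed model per outcome on all participants, with treatment number, response and their interaction. Percent QIDS change may replace the binary response as a continuous modifier.
2. Name the whole-sample slope as the test of the Aim 1 and Aim 2 hypotheses, and say plainly that this model is fitted.
3. Report the between-group slope difference with its confidence interval as exploratory, and give the group slopes descriptively. Base any statement about response on this contrast alone.
4. Allow the slope variance to differ by group, or report a sensitivity analysis. A shared variance is not a harmless assumption with 3 or 4 non-responders.
5. State that power for the contrast is about 0.19 to 0.29 at 17 evaluable if non-responders show no change, and limit the Conclusion's claim about responsiveness accordingly.

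The cost is wording and analysis code, with no new patients, visits or measurements. It does not buy an adequately powered response comparison, which would need roughly 90 to 152 recruited under the assumptions above.
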